**Figure 1 hsr271608-fig-0001:**
[figure not shown]
Consolidated standards of reporting trials flow diagram estimating patient screening, enrollment, and response rate.

### Adverse Events

2.8

This is a low‐risk study; we do not prognosticate any adverse events related to the study intervention (hypnosis). However, the Principal Investigator and the study team will evaluate and promptly address any adverse events. Furthermore, other anticipated issues or events will be evaluated within 72 h, and serious adverse events will be assessed.

### Equipment

2.9

#### Data Collection Tools

2.9.1

In this study, the level of patient resilience will be measured as the primary outcome using the Connor‐Davidson Resilience Scale (CD‐RIS). The reliability and validity of the Persian Resilience Scale have been investigated and validated in preliminary studies in patient and normal samples. Mohammadi used Cronbach's alpha coefficient; the reliability scale reached 0.89, and the worth of each item alongside the overall score using the correlation coefficient ranged from 0.41 to 0.64 [47]. Samani and Sahragard, in a study on students in Shiraz, achieved scale reliability through Cronbach's alpha coefficient of 0.87 [48].

Additionally, the quality of life of the patients (as the secondary outcome) will be measured using the PCOS Health‐Related Quality of Life Questionnaire (PCOSQ). Amini et al. showed that the Iranian version of PCOSQ has acceptable validity and reliability and is an appropriate tool for measuring the quality of life of patients with polycystic ovary syndrome. To assess the reliability of the questionnaire, they employed the method of evaluating the internal consistency of the instrument. The findings demonstrate that the Cronbach's alpha coefficient for the entire questionnaire was 0.90, for emotional aspects it was 0.80, for hirsutism it was 0.87, for weight it was 0.77, for infertility issues it was 0.84, and for menstrual issues it was 0.52. In addition to testing the validity of the questionnaire, a type of validation, namely item‐level correlation and comparison between known groups, was used. So, each question shows the highest correlation coefficient with its relevancy domain, and all coefficients are greater than 0.4 [49].

Eventually, their anxiety and depression (as the secondary outcome) will be evaluated using the Hospital Anxiety and Depression Scale (HADS). Kaviani et al. showed in their research that the HADS scale and subscales of anxiety and depression have good validity, reliability, and internal consistency with a Cronbach's alpha coefficient of 0.07 for the seven items of the depression scale, and 0.85 for the seven items under the anxiety scale [50].

#### Data Management

2.9.2

To complete the questionnaires, participants will be given randomly assigned ID numbers. Separate linking lists containing names and ID numbers will be kept confidential on a server that can only be accessed by project members and Systems Administrators (who are trained in conducting ethical research with human participants). Upon completion of the project and verification of the data, the linking list will be destroyed, and the data will become anonymous. The study coordinator, who is not blinded to the randomization, will document recruitment, attrition, and safety. Study data will consistently be kept securely, either in a locked cabinet or on computers with password protection, accessible only to study team members.

### Interventions

2.10

After allocating the samples to two control and intervention groups, they will be provided with the questionnaires. Then, patients of both groups receive standard treatments related to women with PCOS (including oral contraceptives, spironolactone, and metformin) [30, 51] and will be visited and treated by a gynecologist. Patients will also be recommended to follow a diet of their choice with an intake of 1500–1800 kcal per day [29], as well as a gentle aerobic exercise activity of 150 min per week [52] during the study. In addition, they should not use other relaxation methods and counseling sessions during the research. Also, the participants will be asked not to use cosmetic procedures (including laser and Botox, etc.) during the study, and they will be asked in each session, and if they are used, it will be recorded.

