### Objectives

2.1

The primary objective of this study is to assess the impact of hypnotherapy on the resilience of individuals suffering from polycystic ovary syndrome (PCOS). The particular aims of this study are to assess and contrast the levels of resilience, quality of life, anxiety, and depression in both the control and intervention groups before the intervention, right after the intervention, and 4 weeks post‐intervention.

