### Blinding

2.7

It will be impossible to keep participants blind during the intervention process, as a result of the nature of the intervention [44]. Blinding will be done at the assessor level [45]. In this way, after concluding the work, the research colleague hands over the questionnaires to the samples, and after completing the questionnaire, a box will be placed there, and the participants will put the completed questionnaire in the box. Groups are named A and B. The statistical analyst is also blinded, and at the end of the analysis, the coded groups will be identified [44, 45, 46]. Figure 1 is the CONSORT flow diagram and includes the calculation of the numbers of eligible, screened, enrolled, and analyzed participants.

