#### Hypnotherapy Intervention Group

2.10.1

In the intervention group, hypnotherapy is performed by a qualified researcher who is certified by the Iranian Association of Clinical Hypnosis and holds a valid credential. For every participant in the intervention group, there will be 6 weekly hypnotherapy sessions lasting 40–60 min each (Table 1).

**Table 1 hsr271608-tbl-0001:** The content of six hypnotherapy sessions.

Sessions	The subject matter of the session
First	Taking a history, fully explaining how to do the work, educating and preparing the patient, eliminating the misunderstanding of hypnosis, and completing the questionnaires (Patients are also asked to describe a place in the real world that gives them a sense of safety and comfort).
Second	Induction and deepening, and direct instincts to increase relaxation and conditioning for rapid hypnosis in the next sessions.
Third	Strengthening the ego to increase self‐esteem and increase the endurance and resilience to life issues in the individual.
Fourth	Age regression and dealing with negative emotions, and then increasing calmness.
Fifth	Age progression and conditioning to improve lifestyle.
Sixth	Reviewing the previous sessions, the mental experience of a favorable physical feeling, and focusing on increasing relaxation in the whole body and mind. Completing the questionnaires again.

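### The baseline questionnaires come after unblinded allocation, so scores labelled pre-intervention are open to a difference between arms caused by the assignment itself

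*Protocol article*

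**What the plan says.** The Objectives (2.1) set three measurement times for resilience, quality of life, anxiety and depression: "before the intervention, right after the intervention, and 4 weeks" after it. Statistical Analysis (2.13) uses the first of these as one of three repeated measures of resilience, and Testing of the Hypothesis (2.14) describes it in the same terms.

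The Interventions section (2.10) places the first questionnaires after allocation: "After allocating the samples to two control and intervention groups, they will be provided with the questionnaires". The next sentence begins "Then, patients of both groups receive standard treatments related to women with PCOS", so this administration is the baseline one.

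Table 1 (2.10.1) lists the questionnaires within hypnotherapy session 1: "educating and preparing the patient, eliminating the misunderstanding of hypnosis, and completing the questionnaires". The same cell adds, in brackets, "Patients are also asked to describe a place in the real world that gives them a sense of safety and comfort". Session 6 closes with "Completing the questionnaires again", which confirms session 1 as the earlier administration. The Control Group section (2.10.2) has controls measured at the same times.

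On blinding, section 2.7 says: "It will be impossible to keep participants blind during the intervention process". The Sampling section (2.5.2) describes only a coded list of eligible women, and Random Allocation (2.6) uses only marital status and BMI. No section describes a questionnaire completed before randomisation.

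**The concern.** A baseline score is useful because the assignment cannot have affected it. Here each score is the woman's own report, and it is collected after her arm has been drawn. In the hypnotherapy arm, as Table 1 has it, it is collected at a session she attends because of that arm. Expectation among women assigned hypnotherapy, or disappointment among controls, could move the answers. Blinding the assessor and the analyst does not help, because the participant is the rater.

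Group-by-time and change estimates subtract this score, and a baseline-adjusted estimate conditions on it. A shift that is present at baseline and fades by follow-up would enter all three. In addition, a baseline difference in CD-RIS, PCOSQ or HADS could no longer be read as chance imbalance, so these scores would not serve as a check on randomisation.

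**Working it through.** **1. Order of events.** Sections 2.5.2, 2.6, 2.10 and Table 1, read together, give: coded eligibility list, allocation, questionnaires (session 1 in the hypnotherapy arm, the same time in controls), then treatment. The measurement precedes standard treatment but follows allocation. Hypnotic induction first appears in session 2, so what could act within session 1 is history taking, explanation, education and the safe-place request.

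**2. Planning figures (2.5.1).** Control 48.17 ± 20.61; intervention 69.80 ± 23.38; type 1 error 0.05; power 0.90; attrition 20%.

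- Difference = 69.80 − 48.17 = 21.63.
- Pooled SD = √((20.61² + 23.38²)/2) = 22.04.
- n per group = 2 × (22.04 × (1.960 + 1.282)/21.63)² = 21.8, so 22 per group, as stated.
- 44/0.80 = 55, made even = 56, as stated.

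The sample size is reproduced and is not in question. The figures serve only to put a scale on the bias.

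**3. Form of the bias.** Let *b* be the assignment-induced difference at baseline (hypnotherapy minus control), *p* the fraction of it still present at follow-up, and τ the follow-up difference apart from that shift.

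- Change estimate = (τ + *pb*) − *b* = τ − (1 − *p*)*b*.
- If *p* = 0 the bias is −*b*; if *p* = 1 the shift cancels.
- Baseline-adjusted estimate with *p* = 0 and correlation ρ: τ − ρ*b*.

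**4. Direction.** Higher scores from expectation under hypnotherapy make *b* positive. Lower scores from disappointment in controls also make *b* positive. The two add, and both understate benefit. The sign reverses only if controls score higher, or hypnotherapy women lower, because of the assignment.

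**5. Size, for illustration.** The documents give no value for *b*, *p* or ρ. Assumed: *b* of 0.1 to 0.3 SD, *p* = 0, ρ = 0.5.

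| Assumed shift | Points (× 22.04) | Change bias, share of 21.63 | Adjusted bias (0.5 × shift) |
|---|---|---|---|
| 0.1 SD | 2.2 | 10% | 1.1 points |
| 0.2 SD | 4.4 | 20% | 2.2 points |
| 0.3 SD | 6.6 | 31% | 3.3 points |

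**6. Effect on the test.** Take 22 women per arm, no true effect and ρ = 0.5. The SD of change is 22.04 × √(2 × 0.5) = 22.04, and the standard error is 22.04 × √(2/22) = 6.64. By the normal approximation, a two-sided 5% test of change then rejects about 6%, 10% and 17% of the time for the three shifts. Over ρ from 0.3 to 0.7 the range is about 6% to 25%.

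**The case against.** A reader might infer that the baseline of every outcome is already contaminated. The documents do not show that. They establish the order of events, not a shift, and its size and direction are unknown. Nor do they say when controls learn their arm; section 2.7 speaks of blinding during the intervention process, so disappointment among controls at baseline is an inference.

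A reader might also infer that the questionnaire is the last step of session 1 and follows all its teaching. Table 1 gives the subject matter of each session and fixes no order within it; the safe-place request is even printed after the questionnaires. Section 2.10 taken alone could mean a hand-out between allocation and the first session. With induction starting only in session 2, the session-content route is clearly the weaker one. None of these readings moves the measurement ahead of allocation.

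The size rests on assumption. The 10% to 31% restates 0.1 to 0.3 SD against a planned difference of 21.63/22.04 = 0.98 SD, and it needs the shift to have gone by follow-up. A shift that persisted in full would cancel from a change estimate.

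The damage also has limits. Demographic variables and the two stratifiers are not plausibly altered by learning one's arm, so they still check the randomisation. The two-sample tests in section 2.13 can compare follow-up scores without any baseline. Section 2.16 discloses probable bias from awareness and self-report, though it does not mention baseline timing.

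All these limits stand. They narrow the claim but leave the sequence itself unanswered.

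**Conclusion.** The point holds as a design weakness: the scores that the plan labels pre-intervention are collected after unblinded allocation, and the protocol describes no earlier measurement. CD-RIS, PCOSQ and HADS at baseline are open to an assignment-induced difference. Knowledge of the arm is the main route and session 1 content a secondary one.

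Bias in the group-by-time, change and baseline-adjusted estimates depends on a shift that is present at baseline and does not persist. Under the mechanism most easily argued, the trial would understate the benefit of hypnotherapy. The illustrative range for CD-RIS is 2.2 to 6.6 points for a change estimate and 1.1 to 3.3 points after baseline adjustment. Both rest on the assumed shift, and the second also on the assumed correlation of 0.5. No comparable figure can be given for PCOSQ or HADS, because the document reports no SD for them. A comparison of follow-up scores alone is unaffected by a baseline shift.

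**What to change.** In section 2.10 and Table 1, have every woman not yet randomised complete CD-RIS, PCOSQ and HADS after consent and before her allocation is drawn or disclosed. Remove the questionnaires from session 1, so that the wording in 2.1, 2.13 and 2.14 becomes true as it stands.

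The Consent section says sampling began in February 2023 and is ongoing. Flag the women already measured after allocation, report how many there are in each arm, and add a sensitivity analysis that compares follow-up scores between arms without using baseline. The sample size was itself derived from a two-group comparison of means without baseline, so under the plan's own assumptions 22 analysed per group still gives that comparison about 90% power.

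The cost is a short amendment under section 2.12. It needs no extra visits, staff or patients, and the total stays at 56. The small downside is two baseline regimes within one 56-woman trial, which the flag and the sensitivity analysis make visible.

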#### Hypnotherapy Intervention Group

2.10.1

In the intervention group, hypnotherapy is performed by a qualified researcher who is certified by the Iranian Association of Clinical Hypnosis and holds a valid credential. For every participant in the intervention group, there will be 6 weekly hypnotherapy sessions lasting 40–60 min each (Table 1).

**Table 1 hsr271608-tbl-0001:** The content of six hypnotherapy sessions.

Sessions	The subject matter of the session
First	Taking a history, fully explaining how to do the work, educating and preparing the patient, eliminating the misunderstanding of hypnosis, and completing the questionnaires (Patients are also asked to describe a place in the real world that gives them a sense of safety and comfort).
Second	Induction and deepening, and direct instincts to increase relaxation and conditioning for rapid hypnosis in the next sessions.
Third	Strengthening the ego to increase self‐esteem and increase the endurance and resilience to life issues in the individual.
Fourth	Age regression and dealing with negative emotions, and then increasing calmness.
Fifth	Age progression and conditioning to improve lifestyle.
Sixth	Reviewing the previous sessions, the mental experience of a favorable physical feeling, and focusing on increasing relaxation in the whole body and mind. Completing the questionnaires again.

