#### Sample Size

2.5.1

According to Fathi et al.'s study [41], the average resilience in the control group was 48.17 ± 20.61, and in the intervention group was 69.80 ± 23.38. By applying these findings and taking into account a type 1 error of 0.05 and a test power of 0.90, the sample size for every group was calculated using the following formula:

Therefore, 22 people in each group and a total of 44 people will enter the study. But considering that in this study, resilience is measured in three stages (before the intervention, right after the intervention, and 4 weeks post‐intervention). The samples may have dropped. For this problem, the final sample volume was determined with a 20% drop:

The total sample size was 55, considering the 20% attrition, and as regards, we have two groups, so we considered the total sample size to be 56 people. Therefore, 28 samples are included in the study in each group (intervention and control).

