#### Control Group

2.10.2

For the control group, routine care will be done (Routine care means receiving standard treatments by a gynecologist and balanced physical activity and diet).

Questionnaires will be done simultaneously with the intervention group at all stages.

Participants' records will be organized numerically and kept in a secure, easily accessible way and location. Records of participants will be maintained for 2 years following the conclusion of the study.

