### Protocol Deviation

2.11

Deviations or protocol violations may have occurred in this study and will be reported. An instance of deviation in a procedure is a follow‐up appointment occurring at a slightly varied time frame than mandated by the protocol; patients with these deviations will be incorporated into the intention‐to‐treat analysis. All study subjects randomly assigned to the studied groups during randomization processes, regardless of the type of intervention received during the study, their violation of protocol, discontinuation, and withdrawal from participating in the study, as well as all cases that occurred after randomization, will be included in the intention‐to‐treat analysis.

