### Statistical Analysis

2.13

The data from quantitative variables will be described by calculating the mean ± standard deviation, and qualitative variables will be described in terms of frequency and percentage. To compare variables between intervention and control groups according to the qualitative and quantitative variable nature, the *χ*
^2^ test (if the default is not established, Fisher's exact test) and *t*‐test of two independent samples, analysis of variance, or its non‐parametric equivalent (Mann–Whitney and Kruskal–Wallis) will be used, respectively. It should be noted that checking the defaults in terms of normality (Kolmogorov–Smirnov and Shapiro–Wilk test) and equality of variances (Levene and F test) will be on the agenda. Finally, to compare the mean resilience score between the two intervention and control groups during the study period (before the intervention, right after the intervention, and 4 weeks post‐intervention), and also to control for the effect of intervening factors, repeated measures ANOVA or mixed models will be used for variance analysis. For every outcome, the projected effect size along with its 95% confidence interval will be displayed. The significance level of the tests will be 0.05. The analysis will be conducted using SPSS V.26. The reporting of statistical results will adhere to the Statistical Analyses and Methods in the Published Literature (SAMPL) guideline [53].

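### Post-treatment questionnaires are placed inside hypnotherapy session six, with no stated route for measuring women who stop earlier, although discontinuers are promised in the intention-to-treat analysis

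*Protocol article*

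**What the plan says.** Outcomes are due before the intervention, right after it and 4 weeks later (protocol article, section 2.1; also 2.13 and 2.14). In the hypnotherapy arm, the only place given for the second measurement is the last line of Table 1 in section 2.10.1, where the content of session six ends with "focusing on increasing relaxation in the whole body and mind. Completing the questionnaires again". The same table puts the first completion in session one. The 4-week measurement is not listed in any session.

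For controls, section 2.10.2 says: "Questionnaires will be done simultaneously with the intervention group at all stages". Section 2.7 describes the hand-over: "after concluding the work, the research colleague hands over the questionnaires to the samples". The women then put the completed forms in a box on the spot. Neither section mentions women who have stopped attending.

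Section 2.11 includes everyone randomised in the intention-to-treat analysis, "regardless of the type of intervention received during the study, their violation of protocol, discontinuation, and withdrawal from participating in the study". Section 2.13 leaves the main analysis open: "repeated measures ANOVA or mixed models will be used for variance analysis".

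**The concern.** Section 2.11 says who is to be analysed, but it does not collect any data. Read as written, the only stated occasion for the post-treatment resilience (CD-RIS), quality of life (PCOSQ) and anxiety and depression (HADS) scores in the hypnotherapy arm is a treatment session. A woman who stops after, say, session three does not reach it. Stopping treatment and missing the outcome can then become one event, through a mechanism that controls, who receive no hypnotherapy, do not share.

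Women who stop a psychological treatment early may be those who are gaining least. If their scores are missing for that reason, the post-treatment difference would favour hypnotherapy on the primary outcome and possibly on the secondary ones. A statistical analysis plan can choose how to handle missing scores, but it cannot recover scores that were never collected. The Consent section describes recruitment as ongoing, so the gap matters while women are still being treated.

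**Working it through.** **1. The plan's own figure.** Section 2.5.1 gives these planning values: "the average resilience in the control group was 48.17 ± 20.61, and in the intervention group was 69.80 ± 23.38". It sets type 1 error at 0.05, power at 0.90 and a 20% allowance for loss.

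- Difference: 69.80 − 48.17 = 21.63.
- Pooled SD: √[(20.61² + 23.38²)/2] = 22.04, so the standardised difference is 21.63/22.04 = 0.98.
- n per group = 2 × [22.04 × (1.960 + 1.282)/21.63]² = 21.8, rounded up to 22. Sidedness is not stated; two-sided reproduces the plan's figure, while one-sided would give 18.
- Total 44; 44/0.8 = 55, rounded to 56, or 28 per group.

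The stated sample size reproduces.

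**2. Is power the issue?** No. If a 20% loss fell on the hypnotherapy arm alone (22 against 28 analysed), t-test power at the planned difference would still be about 92%.

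**3. Size of a possible bias.** Let q be the share of the hypnotherapy arm not measured after treatment, and g the gap in mean score between completers and stoppers, in SDs. If only completers are analysed:

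completer mean − mean of all randomised = q × g × SD

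Both q and g are assumptions. With SD 22.04, the overstatement in points is:

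| Unmeasured (q) | g = 0 | g = 0.5 SD | g = 1 SD |
|---|---|---|---|
| 10% | 0 | 1.1 | 2.2 |
| 20% | 0 | 2.2 | 4.4 |
| 30% | 0 | 3.3 | 6.6 |

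For example, 0.20 × 0.5 × 22.04 = 2.2 and 0.20 × 1 × 22.04 = 4.4.

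**4. Effect on the test.** With no true difference between the arms as randomised, and 22 against 28 analysed at q = 20%, the chance of a significant result is about 6.4% for a 0.5 SD gap and about 10.6% for a 1 SD gap, against a nominal 5%.

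**5. What the choice of model does.** Repeated measures ANOVA in its usual form drops any woman with a missing visit, so it behaves like the complete-case calculation above. A mixed model keeps a woman with baseline and 4-week scores and uses them to inform the missing one. That reduces the bias so far as those scores explain why she stopped, and leaves the remainder.

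**The case against.** The strongest reply is that the article nowhere makes attendance a condition of measurement. Table 1 is a description of session content and omits the 4-week assessment altogether. The hand-over in section 2.7 is by a colleague, not the therapist. Section 2.11 expressly keeps discontinuers in. Sessions are weekly over a six-week course and controls are measured at the same times, so the timing is already close to calendar-based. How discontinued women are contacted could sit in the full protocol, which is not shown.

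Much of this stands, and it limits the point. A reader might infer that the intention-to-treat result necessarily becomes a completer result. The article does not support that: it never says that stoppers are excluded or left unmeasured, the 4-week measurement is not tied to a session, and mixed models are allowed.

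A reader might also infer that controls cannot lose measurements in any comparable way. Sections 2.10 and 2.15 speak of asking participants, apparently in both groups, about cosmetic procedures, diet and exercise at each session. Controls may therefore have contacts of their own that they could miss.

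Finally, a reader might take the effect to be overstated by 25% at the plan's own 20% allowance (21.63 reported against 0.8 × 21.63 = 17.30). That needs every stopper to be unmeasured and to gain nothing, and only completers to be analysed. The 20% in section 2.5.1 covers loss over three measurements and is not split by arm; it is not a rate of stopping hypnotherapy.

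The reply does not remove the core. The one stated occasion for the post-treatment measurement in the hypnotherapy arm is session six, the hand-over in section 2.7 is in person at the end of the work, and no section gives a woman who has stopped attending another way to be measured then. This is not mere missing detail, because what is written places the measurement where a discontinuer will not be.

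**Conclusion.** The point holds as a weakness in how the post-treatment measurement is scheduled. It is not a demonstrated bias. Section 2.10.1 places that measurement in a treatment session, section 2.11 promises to include women who will not reach it, and the two need to be reconciled.

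Harm requires two conditions that the article neither states nor rules out: that stoppers go unmeasured at that time point, and that they differ from completers. Under a complete-case analysis with 20% of the hypnotherapy arm unmeasured, the overstatement lies between 0 and about 4.4 points for gaps of 0 to 1 SD. Even the upper end is about a fifth of the planned difference (4.4/21.63 = 20%). The 4-week comparison is less exposed, although the article gives no date for it when a woman has stopped early. This is a cheap improvement worth making while recruitment continues.

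**What to change.** Reconcile section 2.10.1 with section 2.11 as follows:

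- Time both post-baseline assessments from randomisation, with the same target dates in both arms: the planned end of the six-week course and 4 weeks after that. Take questionnaire completion out of the content of session six.
- State that a woman who stops hypnotherapy remains in the study and is offered the questionnaires on both dates unless she withdraws consent to data collection.
- Record the number of sessions attended separately from withdrawal from the study.
- In section 2.13, settle on the mixed model, so that women with one missing visit are kept.

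The cost is a short amendment and a little extra effort to reach women who stop sessions. The sample size of 56 is unchanged.
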